## Abstract

**Background:**

Coronary heart disease (CHD) is the leading cause of deaths and disability worldwide. Cardiac rehabilitation (CR) effectively reduces the risk of future cardiac events and is strongly recommended in international clinical guidelines. However, CR program quality is highly variable with divergent data systems, which, when combined, potentially contribute to persistently low completion rates. The QUality Improvement in Cardiac Rehabilitation (QUICR) trial aims to determine whether a data-driven collaborative quality improvement intervention delivered at the program level over 12 months: (1) increases CR program completion in eligible patients with CHD (primary outcome), (2) reduces hospital admissions, emergency department presentations and deaths, and costs, (3) improves the proportion of patients receiving guideline-indicated CR according to national and international benchmarks, and (4) is feasible and sustainable for CR staff to implement routinely.

**Methods:**

QUICR is a multi-centre, type-2, hybrid effectiveness-implementation cluster-randomized controlled trial (cRCT) with 12-month follow-up. Eligible CR programs (*n* = 40) and the individual patient data within them (*n* ~ 2,000) recruited from two Australian states (New South Wales and Victoria) are randomized 1:1 to the intervention (collaborative quality improvement intervention that uses data to identify and manage gaps in care) or control (usual care with data collection only). This sample size is required to achieve 80% power to detect a difference in completion rate of 22%. Outcomes will be assessed using intention-to-treat principles. Mixed-effects linear and logistic regression models accounting for clusters within allocated groupings will be applied to analyse primary and secondary outcomes.

**Discussion:**

Addressing poor participation in CR by patients with CHD has been a longstanding challenge that needs innovative strategies to change the status-quo. This trial will harness the collaborative power of CR programs working simultaneously on common problem areas and using local data to drive performance. The use of data linkage for collection of outcomes offers an efficient way to evaluate this intervention and support the improvement of health service delivery.

**Ethics:**

Primary ethical approval was obtained from the Northern Sydney Local Health District Human Research Ethics Committee (2023/ETH01093), along with site-specific governance approvals.

**Trial registration:**

Australian New Zealand Clinical Trials Registry (ANZCTR) ACTRN12623001239651 (30/11/2023) (https://anzctr.org.au/Trial/Registration/TrialReview.aspx?id=386540&isReview=true).

## Background

Cardiovascular disease (CVD) is the leading cause of death globally, with coronary heart disease (CHD) accounting for nearly one-fifth of total deaths [1]. About 10% of people who survive a myocardial infarction experience another acute cardiac event within the first year [2], most of which are largely preventable [3, 4]. Comprehensive cardiac rehabilitation (CR) including structured exercise, psychosocial care, and timely patient education focussed on support for a healthy lifestyle and medication adherence is a cornerstone of care for patients with CHD [5, 6]. Patients who complete CR reduce their risk of repeat myocardial infarction (RR 0.72, 95% CI 0.55–0.93) and all-cause hospital admissions (RR 0.58, 95% CI 0.43–0.77) [7] accompanied by clinically meaningful improvements in functional capacity and health-related quality of life (HRQL) [7, 8]. Despite these benefits and strong recommendation of CR for the secondary prevention of CHD in international guidelines (Class 1 A evidence) [9], program participation rates continue to be suboptimal [10–12]. 

Poor attendance and completion of CR programs mean that many eligible patients fail to achieve the potential benefits of these programs. For instance, studies have demonstrated a dose-response benefit between exercise sessions attended and reductions in all-cause mortality [13] and risk of major adverse cardiovascular events (MACE) [14]. To achieve these benefits, it is recommended that CR programs offer a sufficient dose of exercise and efforts should focus on enabling patients to adhere to all prescribed sessions. Despite this, CR participation rates remain poor worldwide, with average rates ranging from 26.9% [10] to 48% [11]. Barriers to CR participation have been identified and include a combination of factors, both organisational (such as lack of adequate space and equipment) [15], and patient (such as not prioritising CR attendance amongst other life demands) [16]. There is growing evidence that suggests the quality of the CR program likely influences patient participation and thus outcomes [17]. National audits using quality indicators, performance measures, and key performance indicators (KPIs) developed by international peak bodies provide a means to evaluate the implementation of guideline-recommended therapies [18–21]. For instance, an audit of 170 programs in the United Kingdom found only 30.6% were considered high-quality according to their pre-determined minimum standards for CR (defined as having multidisciplinary team, offered to priority patient groups, and of adequate duration) [22]. In this audit, 5.3% does not meet any of the minimum standards and thus unlikely to facilitate patient participation or optimise outcomes [22]. Improving CR program quality may therefore be one of the keys to addressing low patient participation and completion.

One way to improve patient participation and completion of CR is by drawing on a Collaborative Quality Improvement Methodology, where various stakeholders work together toward a common goal of improving performance using a defined set of quality measures [23]. This collaborative approach enables rapid and sustainable changes in service delivery and, thus, has the potential to leverage the collective power of CR programs working simultaneously on shared problems and using data to drive performance [23]. Collaborative quality improvement has been successfully used in general practice [24], as well as in the management of asthma [25], and chronic heart failure [26], but to our knowledge, has not been tested for the optimal delivery of CR. Although a strategy of using purposeful and planned quality improvement initiatives demonstrated significant increase in patient attendance and completion in CR [27], this study was single-centre and non-randomized. Therefore, more evidence on the benefits of these initiatives is needed using robust research designs.

The Quality Improvement in Cardiac Rehabilitation (QUICR) trial aims to determine whether the implementation of a 12-month data-driven collaborative approach, relative to usual care:

increases CR program completion of patients with CHD (primary outcome),reduces unplanned hospital admissions, emergency department presentations and deaths, and associated costs, and.improves the proportion of patients receiving guideline-indicated CR according to national and international benchmarks, and 

Furthermore, QUICR will include a process evaluation that runs parallel to the trial. This process evaluation will investigate the implementation of the collaborative approach and explore whether it is feasible and sustainable for CR staff to implement routinely, and identify enablers and barriers to implementation.

## Methods

This trial protocol follows the Standard Protocol Items: Recommendations for Interventional Trials (SPIRIT) checklist [28] and QUICR will be conducted in accordance with the Consolidated Standards of Reporting Trials (CONSORT) extension for cRCTs [29]. 

### Study Design

A type-2 hybrid effectiveness-implementation study [24], which uses a 2-arm, multi-centre, cluster-randomized controlled trial (cRCT) design will be conducted over 12 months (Fig. 1). The cRCT design enables accurate confirmatory causal inference [30]. The type-2 hybrid effectiveness-implementation study design, which has a dual focus on effectiveness and implementation outcomes, allows for simultaneous evaluation of the implementation intervention/strategy during an effectiveness trial [31]. 

**Fig. 1 Fig1:**
[figure not shown]
The QUICR Trial flow diagram

### Study Setting/Recruitment

CR programs across two Australian states (New South Wales and Victoria) will be identified through our existing professional networks, societies, and available CR directories [32]. The research team will approach potential CR program leaders and provide information about the trial via email and/or phone call and during state-based in-person/online CR events. CR program leaders will be invited to ask questions and discuss any potential barriers to participation. Research team members will coordinate expressions of interest to participate, confirm eligibility, and commence formal recruitment processes.

### Program Eligibility Criteria

CR programs will be eligible to participate if they:

enrol at least 70 patients eligible for CR per year,have internet-enabled computers, and.have staff with access to and proficiency in using the REDCap electronic collection data platform.

CR programs will be excluded if they are:

unwilling to provide written agreement to participate in the quality improvement intervention or.already participating in a structured research project that entails changes to their usual CR program delivery.

The patient cohort for QUICR will comprise a dataset of all consecutive patients enrolled in participating CR programs who are ≥ 18 years old with a documented diagnosis of CHD in the medical record.

### Study outcomes

Table 1 outlines the QUICR KPIs. The primary outcome is CR program completion, defined as participation in ≥ 80% of sessions of the usual 6-8-week program. Secondary outcomes include: (1) unplanned hospital admissions, emergency department presentations and deaths, and associated costs via analysis of linked administrative data, (2) proportion of patients receiving guideline-indicated CR according to national and international benchmarks (e.g. assessment of risk factors, exercise capacity, medication adherence, and HRQL at entry and completion, and documented discharge transition plan), and (3) enablers and barriers to implementation of the QUICR intervention.

**Table 1 Tab1:** QUICR Key Performance Indicators

1. Program completion
2. Wait time
3. Exercise capacity
A. Proportion of patients assessed for exercise capacity scores at initial assessment
B. Proportion of patients assessed for exercise capacity scores at completion assessment
C. Proportion of patients achieving improvement in exercise capacity
4. Low-density lipoprotein cholesterol (LDL-C)
A. Proportion of patients checked for LDL-C
5. Medication adherence
A. Proportion of patients assessed for medication adherence at initial assessment
B. Proportion of patients currently adhering to medication regimen at initial assessment
C. Proportion of patients assessed for medication adherence at completion assessment
D. Proportion of patients currently adhering to medication regimen at completion assessment
E. Change in proportion of patients currently adhering to medication regimen
6. Smoking
A. Proportion of patients assessed for smoking at initial assessment
B. Proportion of patients currently smoking offered/referred for smoking cessation counselling
C. Proportion of patients assessed for smoking at completion assessment
D. Proportion of patients currently smoking
E. Change in proportion of patients currently smoking
7. Depression
A. Proportion of patients screened for depression at initial assessment
B. Proportion of patients positive for depression offered/referred for counselling
C. Proportion of patients screened for depression at completion assessment
D. Proportion of patients positive for depression at completion assessment
E. Change in proportion of patients positive for depression
8. Health-related quality of life (HRQL) using EQ-5D-5 L
A. Proportion of patients assessed for HRQL at initial assessment
B. Proportion of patients assessed for HRQL at completion assessment
C. Proportion of patients achieving improvement in HRQL
9. Ongoing management plan
A. Proportion of patients with documented ongoing management plan for patient and GP
10. Patient experience survey
A. Proportion of patients who completed the patient experience survey

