### Intervention and control groups

#### Intervention Group

CR programs allocated to the intervention arm will participate in a multicomponent, data-driven quality improvement intervention (Table 2). The intervention is designed to use local CR data to drive small, progressive changes using Plan-Do-Study-Act (PDSA) cycles [33] aligned to pre-determined KPIs (Table 1). These indicators have been selected using national and international benchmarks of quality [18–21] and were developed and approved through an iterative process involving the trial investigators, CR clinicians, quality improvement experts, and consumers. The intervention will be guided by the Model for Improvement [34] using streamlined data entry and regular visual reports to programs via purpose-built databases using software systems REDCap and Microsoft PowerBI and underpinned by principles of collaboration and support. CR program leaders will collaborate in an ongoing way over 12 months supported and facilitated by the research team.

**Table 2 Tab2:** Components of the QUICR collaborative quality improvement intervention

1. **QUICR Dashboard and Monthly Reports**
Patient data entered into REDCap will be automatically extracted into a specially developed QUICR Dashboard to generate visual summaries of KPIs assessed and benchmarked against other participating programs anonymously. These monthly reports will provide CR program leaders accurate updates on their program’s performance in relation to KPIs over time.
2. **Collaborative Quality Improvement**

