#### Control Group

CR programs allocated in the control arm are to provide usual care to their patients. For the purpose of measuring change in primary and secondary outcomes of intervention sites relative to control sites, staff working in CR at control sites are required to enter patient data into the purpose-built REDCap data collection platform. They will not have access to any of the abovementioned QUICR resources. These materials will be provided to the control group following trial completion.

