### Data Collection and Management

All data will be collected at baseline, 12, and 24 months. The primary endpoint is 12 months. Individual patient-level data will be collected by CR program staff as part of routine care. De-identified demographic and CR patient outcomes data including costs will be entered into a purpose-built login-protected REDCap data collection platform hosted by the University of Sydney [35]. The master coding sheet with full patient identifiers will remain at each CR site’s server and will be the responsibility of the data custodian nominated at each program. Coding is crucial for this trial to enable access to and analyse administrative data for linkage. Data extracted to the QUICR Dashboard will be aggregated and automatically converted to visual form and no individual data point will be traceable. The QUICR Dashboard will also be login-protected, to which only a select number of the research team will have access.

Unplanned hospital admissions, emergency department presentations, and deaths will be collected via state-based linked administrative data. Probabilistic matching will be used to link records and the estimated proportion of invalid and missed links using data linkage is expected to be very low [36]. 

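### KPIs 7B and, less strongly, 6B are measured among patients found by screening that the intervention targets, so comparing them between arms is not a randomised comparison

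*Protocol article*

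**What the plan says.** Table 1, under Study outcomes in the protocol article, lists two pairs of linked indicators.

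- Depression: 7A is "Proportion of patients screened for depression at initial assessment" and 7B is "Proportion of patients positive for depression offered/referred for counselling".
- Smoking: 6A is "Proportion of patients assessed for smoking at initial assessment" and 6B is "Proportion of patients currently smoking offered/referred for smoking cessation counselling".

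The same section makes the "proportion of patients receiving guideline-indicated CR according to national and international benchmarks" a secondary outcome. Under Intervention Group, Table 2 describes a dashboard that will "generate visual summaries of KPIs assessed and benchmarked against other participating programs anonymously", with monthly reports to program leaders. The Control Group section withholds these resources from control programs until the trial ends. It explains why control staff still enter data: "For the purpose of measuring change in primary and secondary outcomes of intervention sites relative to control sites". On who ascertains patient status, Data Collection and Management says: "Individual patient-level data will be collected by CR program staff as part of routine care". Under Program Eligibility Criteria, the patient cohort is every consecutively enrolled adult with documented CHD.

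**The concern.** A patient counts in the 7B denominator only after being screened and found positive. Whether that happens depends on how thoroughly the program screens, and 7A is one of the indicators that intervention programs are coached and benchmarked on while control programs are not. The patients behind 7B are therefore selected after randomisation, by a step the intervention is designed to change. The two arms' denominators need not be alike in number or in severity.

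A program that screens selectively may find mainly evident cases and refer most of them. One that screens nearly everyone adds milder cases and may refer a smaller share of a larger group. The indicator could then fall while more patients are offered help. If 7B or 6B is read as a trial outcome between arms, that fall would be taken as poorer care.

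**Working it through.** **Inputs.** The plan gives no screening, prevalence or referral rate, so there is no figure of its own to reproduce on this point. The scale of 660 patients per arm (20 programs × 33) is from Sample size. Every other input is an assumption.

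**Formula.** Let p be the true prevalence, s the share of positives identified and r the referral share among those identified.
- 7B = r
- Referred over all enrolled = p × s × r

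**Illustration.** Assume p = 20%, so 660 × 0.20 = 132 positives per arm; s = 50% control and 90% intervention; r = 80% control and 65% intervention.

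| | Control | Intervention |
|---|---|---|
| Identified | 132 × 0.50 = 66.0 | 132 × 0.90 = 118.8 |
| Referred | 66.0 × 0.80 = 52.8 | 118.8 × 0.65 = 77.2 |
| 7B | 80% | 65% |
| Referred / 660 enrolled | 8.0% | 11.7% |

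7B is 15 points lower in the intervention arm, while about 24 more patients are referred (+3.7 points of all enrolled).

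**When the two measures disagree.** 7B is lower but more patients are referred whenever

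r(control) × s(control) / s(intervention) < r(intervention) < r(control).

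Prevalence cancels. With r(control) = 80% and s(intervention) = 90%:
- s(control) = 30%: 0.80 × 0.30/0.90 = 27%, so the range is 27% to 80%
- s(control) = 50%: 44% to 80%
- s(control) = 70%: 62% to 80%

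**When they do not.** If the extra patients are referred at the same 80%, 7B is 80% in both arms. Referred over all enrolled is then 8.0% against 0.20 × 0.90 × 0.80 = 14.4%. There is no reversal, but 7B does not register the gain.

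**Identical referral behaviour in both arms.** Assume 40% of the 132 positives are severe (52.8) and 60% mild (79.2), with referral of 90% and 50% respectively.
- Control detects 90% of severe and 23% of mild cases: 47.5 + 18.2 = 65.7 identified; 42.8 + 9.1 = 51.9 referred; 7B = 78.9%; 7.9% of all enrolled.
- Intervention detects 90% of both: 47.5 + 71.3 = 118.8 identified; 42.8 + 35.6 = 78.4 referred; 7B = 66.0%; 11.9% of all enrolled.

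Case mix alone lowers 7B here.

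**Check of a composite (assessed and, if positive, referred).** Take an assumed program with 100 enrolled, 95 screened, 19 positive and 15 referred. It scores (76 + 15)/100 = 91%, and with no referrals at all it still scores 76%. A program that screens 40, finds 12 and refers 11 scores (28 + 11)/100 = 39%. Screened negatives dominate, so the composite largely repeats 7A and can rank a program referring nobody above one referring 11. Referred over all enrolled gives 15%, 0% and 11% for these three cases.

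**The case against.** The conditional indicator is legitimate in itself: it asks whether an identified need is acted on. Table 1 prints it beside 7A, so a reader would see a fall in 7B together with a rise in 7A. This supports keeping 6B and 7B for feedback. It does not make the between-arm contrast on 7B a randomised one.

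Table 1 consists of short labels in an article, and the analysis plan, which is not shown, may add definitions and say which KPIs are tested. That stands as a limit. Still, the printed labels set the denominator, and only a redefinition would change it.

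Referral is not among the examples given for the guideline-indicated care outcome, which are assessment and documentation items. This also stands. A reader might infer that 6B and 7B are declared stand-alone between-arm tests, but the article does not say so. The list is only illustrative, however, and both indicators are printed under Study outcomes.

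A reader might also infer that the intervention arm will look worse. The document does not support that: it gives no rates, the reversal needs the newly found patients to be referred less often, and the intervention also feeds back 6B and 7B, which pushes referral up.

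Finally, treating 6B as equal to 7B would go too far. Smoking status may be known from other records without a formal assessment, and the argument about milder cases is specific to depression.

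**Conclusion.** The point holds in a limited form. The 7B denominator is formed after randomisation and can be enlarged by the screening that the intervention targets, so a between-arm comparison of 7B is open to selection. For 6B the same structure applies with less force.

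The direction is not determined. 7B falls if the added patients are referred less often, stays put if they are referred equally often, and would rise if they were referred more often. Under the stated assumptions it can show a 15-point deficit alongside a 3.7-point gain over all enrolled patients. Those sizes illustrate the mechanism and do not predict the trial's result.

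The issue is confined to these secondary indicators. Program completion, its sample size and the linked outcomes do not depend on it.

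**What to change.** In the analysis plan, and in a note to Table 1, define the between-arm version of each referral indicator as the proportion of all enrolled CHD patients who were identified as positive for depression (or as smoking) and were offered or referred for counselling. Count patients not assessed as not referred. Present it beside 6A and 7A, because it reflects detection and referral together. Keep the conditional 6B and 7B for the dashboard, benchmarking and descriptive reporting. Do not use the assessed-and-if-positive-referred composite on its own.

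The cost is one extra analysis per indicator, from the REDCap fields already needed for 6A, 6B, 7A and 7B. The all-enrolled percentages will be low and not comparable with benchmarks built on the conditional definition, which is why both should be reported.

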### Randomization

Each CR program will be randomized 1:1 to intervention (QUICR) or control group, via a computer-generated sequence allocation using simple randomization. CR programs that closely interact with each other were treated as a single cluster to circumvent the likelihood of contamination. Allocation will be stratified 50:50 by location of the programs (urban and regional areas) using SAS v9.4.

